**Figure 2 F2:**
[figure not shown]
Classification of heat illness symptoms. BP, blood pressure.

### Sample size

Sample sizes were calculated for both the primary outcomes to provide at least 80% power at the 5% significance level. Based on heat-related symptoms and illness prevalence of 28.9%^21^ and an estimated intracluster correlation coefficient (ICC) of 0.0122, we calculate that 11 clusters per arm (22 clusters in total) with 70 to 80 households per cluster are needed to detect a 30% relative difference in heat-related illnesses while allowing for a 10% attrition rate. We treat 28.9% as a conservative estimate given the longitudinal nature of the primary outcome, as cumulative prevalence over the surveillance period is expected to exceed this single-time point prevalence. To assess quality of life changes, we estimate that with 11 clusters per arm 60 households per cluster are required based on the variability in baseline WHO Quality of Life Brief tool (WHOQOL-BREF) scores reported in Lodhi *et al*,^22^ which documented an average score of 68 (18.0) to detect a difference of 4 points in quality of life score assuming an ICC of 0.015. As the heat-related illness outcome required the larger sample size, the final enrolment target was set at 70–80 households per cluster, which also provides adequate power for the quality-of-life outcome. To assess physiological heat strain, we calculated that a subsample of eight adults (aged 18 years to 60 years) per cluster (balanced by gender) would be required to detect a 15% change in average heart rate, among those who are exposed to heat stress assuming a baseline of 66±12 bpm,^23^ an ICC of 0.1736 and 90% power. Given the complexity of the assessment process, we anticipate a higher attrition rate in this subset and have inflated the sample size by 30% to 10 individuals.

For binary outcomes, the ICC was derived from an assumed cluster-level prevalence variation of ±10%, with the coefficient of variation (CV) estimated from this range and the ICC subsequently calculated using the relationship ICC=k²×P/(1−P), where k is the assumed between-cluster CV of the prevalence, following Pagel *et al*.^24^ For continuous outcomes, the ICC was estimated as the ratio of between-cluster variance to total variance,^25^ with total variance sourced from reference studies and a minimum between-cluster difference of ±9 units assumed. Each co-primary outcome is independently powered at 80% or above. To control the family-wise type I error rate across the two co-primary outcomes, hypotheses will be tested using a prespecified fixed-sequence (hierarchical) procedure: heat-related illness will be tested first at the two-sided 0.05 level, and quality of life will be tested at 0.05 only if the first test is significant. As each outcome is independently powered, this procedure incurs no loss of power. Quality of life is assessed at three time points per year over 2 years; the cross-sectional calculation above is therefore conservative, as the planned repeated-measures mixed-effects analysis increases precision by combining information across visits.

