### Data collection from subset population

Monthly data will be collected from the subset population to provide detailed insights into heat stress and intervention effectiveness (table 3). This will include assessment of thermal comfort, mental health and heat exposure.

**Table 3 T3:** Schedule of outcome assessments and follow-up activities

Parameter	Time points	Details	Devices/tools	Population/unit
Primary outcomes				
All heat-related illness	Weekly during peak summers	Heat-related illnesses	Weekly community survey, health facility data, community surveillance	All members of included households
Quality of life	Mid of April, July and December for two consecutive years	Quality of life mean score	WHOQOL-BREF* questionnaire	Indexed adults of all included households
Secondary outcomes				
All-cause mortality	Weekly during peak summers	Any mortality occurring within the included clusters	Weekly community survey, health facility data, community surveillance	All members of included households
Hospital visit/hospitalisation	Weekly during peak summers	Any hospital admission or hospital visit occurring within the included clusters	Weekly community survey, health facility data, community surveillance	All members of included households
Indoor Heat Index	Continuous throughout the year	Indoor data loggers	Ibutton, Kestrel Drop D2, Temp-U	All included households
Thermal comfort (home)	Monthly	Self-reported comfort levels	Thermal comfort survey adapted from CHEQ-5‡	Indexed adults randomised for subgroup
UTCI	Continuous throughout summers	Outdoor only	Kestrel Drop D2, Kestrel 5400, HOBO weather station	Overall catchment area
Outcomes measured for subset of population				
Personalised heat exposure	Baseline, Monthly	Occupation, sun exposure, illness history, daily routine	Structured survey tool (adapted from HotHaps) and Temp-U	Indexed adults randomised for subgroup
Physiological strain markers	Continuous throughout summers	Heart rate, sleep cycles, VO₂ max†	Fitbit Inspire 3	Indexed adults randomised for subgroup

Participant compliance will be monitored through spot checks and periodic review of device data. For Fitbit devices, heart rate data will be reviewed, as prolonged absence of heart rate recordings may indicate that the device was not worn. Similarly, iButton and Temp-U data will be checked periodically for implausible temperature spikes or sudden drops, which may indicate non-compliance or incorrect device use.

* WHO Quality of Life Brief tool.

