#### Primary outcome analysis

For each participant, a summary record will be constructed comprising the number of heat-related illness episodes and the number of assessment occasions (or person-time) over which the individual was observed. To assess the intervention effect, a Poisson regression model with cluster-level random intercepts will be used, accounting for intracluster correlation. The number of heat-related illness episodes/events will serve as the numerator, while person-weeks at risk will be used as the denominator. Results will be presented as incidence rate ratios (IRRs) with 95% CIs.

Duplicate reports identified across multiple sources will be flagged in the database using participant ID, household ID, date of onset, symptoms and care-seeking information to ensure that each event is counted only once. Symptoms or events continuing from a previous reporting period will be considered part of the same illness episode. A new episode will be defined as either the onset of symptoms following a symptom-free interval of at least 2 days after the previous episode or the occurrence of additional new symptoms in a participant with ongoing previously reported symptoms. For quality-of-life assessments, changes from year one to year two will be compared across three assessment points per year. Summer and winter quality-of-life scores will also be analysed separately. Results will be reported as adjusted mean differences with 95% CIs.

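### The heat-illness sample size is worked out for a prevalence, apparently with one response per household, but the trial tests an episode rate ratio in all household members

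*Protocol article*

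**What the plan says.** **What was sized.** The Sample size section sets the target as "Sample sizes were calculated for both the primary outcomes to provide at least 80% power at the 5% significance level". For heat illness it starts "Based on heat-related symptoms and illness prevalence of 28.9" (per cent), with "an estimated intracluster correlation coefficient (ICC) of 0.0122" and a 30% relative difference. It arrives at 11 clusters per arm and 70–80 households per cluster after 10% attrition. The ICC comes from a formula for binary outcomes: "the ICC was derived from an assumed cluster-level prevalence variation of ±10" (per cent). The section calls 28.9% conservative because cumulative prevalence should exceed a single-time-point figure. Quality of life is said to need 60 households per cluster, and the section then concludes: "As the heat-related illness outcome required the larger sample size, the final enrolment target was set at 70–80 households per cluster".

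**What is tested.** Table 3 gives the unit for heat illness as "All members of included households", assessed weekly during peak summers; the Population section agrees. Under Primary outcome analysis, "For each participant, a summary record will be constructed comprising the number of heat-related illness episodes" together with observation time. Repeat episodes count, person-weeks form the denominator, and a Poisson model with cluster random intercepts yields an incidence rate ratio.

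**Order of testing.** "heat-related illness will be tested first at the two-sided 0.05 level", and quality of life is tested only if that result is significant.

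**The concern.** The calculation and the test differ in three ways: the unit (household or person), the endpoint (prevalence or repeated episodes) and the effect measure (difference in proportions or rate ratio). The calculation contains no number of members per household, no within-household correlation, no episode rate and no allowance for recurrence. The remark that 28.9% is conservative concerns cumulative prevalence, which is not the quantity analysed.

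Two things are at stake. The reader is told which outcome determines enrolment and what effect is detectable, and neither statement has been shown for the planned analysis. Heat illness is also the gate for quality of life, so its power caps the chance that quality of life is formally tested at all. The plan nevertheless asserts at least 80% power for each outcome.

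**Working it through.** **Inputs from the Sample size section.** p0 = 0.289; p1 = 0.7 × 0.289 = 0.2023; ICC 0.0122; 11 clusters per arm; two-sided 5%; 80% power; 10% attrition. For quality of life: SD 18.0, difference 4, ICC 0.015.

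**Assumed, because the article does not give them.** 4–8 members per household; household ICC r; episode rates; overdispersion.

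**1. The ICC.** Reading ±10 points as two standard deviations gives k = 0.05/0.289 = 0.173. Then k² × p0/(1 − p0) = 0.0299 × 0.289/0.711 = 0.0122, as stated.

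**2. The 70–80 households, with one binary response per household.**
- CV form: c = 1 + (1.96 + 0.84)² × [(p0q0 + p1q1)/m + k²(p0² + p1²)]/(p0 − p1)². At m = 63 this is 1 + 7.84 × [0.3669/63 + 0.003725]/0.007517 = 10.96, so 11 clusters. 63/0.9 = 70. Power from a t distribution with 20 df is 79.9%.
- ICC form: design effect 1 + (m − 1) × 0.0122 in both arms, t with 20 df. m = 71.7, and 71.7/0.9 = 79.7.

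The two forms bracket 70–80. Quality of life by the same t method needs 60.4 households (79.9% power at 60), or 60.4/0.9 = 67.1 after attrition. On this basis heat illness does need more: 63–72 against 60.

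**3. All members counted, outcome still binary.** Replace m by H × h/(1 + (h − 1)r), for H households of h members. CV form, t with 20 df:

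| Members h | r | Households for 80%, before attrition | Power at 63 retained |
|---|---|---|---|
| 4 | 0.1 | 20.5 | 95% |
| 4 | 0.5 | 39.5 | 89% |
| 8 | 0.1 | 13.4 | 97% |
| 8 | 0.5 | 35.5 | 90–91% |
| 4–8 | 0.8 | 52–54 | 84% |

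For r = 0.1–0.5 that is 14–40 households. At 63 households the detectable reduction is about 22–27%, not 30%. The ICC form gives 15–45 households and 86–95% power. In that form the need reaches the 60 for quality of life at r of about 0.8.

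**4. Episode rates with recurrence.** The variance of a cluster mean is λ/(Hh) + ωλ²[(1 − s)/(Hh) + s/H] + k²λ², where ω is the squared person-level CV and s is the share of it common to a household. The rate ratio is 0.70. With ω = 4, s = 0.5, H = 63:

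| Control episodes per person | Members h | Power | Households for 80% |
|---|---|---|---|
| 0.289 | 4 | 76% | 75 |
| 0.289 | 6 | 80% (79.6%) | 65 |
| 1.0 | 4 | 81% | 60 |
| 1.0 | 6 | 83% | 55 |

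In the first two rows heat illness needs more households than quality of life.

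**5. Limit set by the number of clusters.** With unlimited households only k²λ² remains, so the noncentrality is 0.30/(k × √(1.49/11)), where 1.49 = 1 + 0.7². Power of 80% on 20 df requires 2.945, which gives k = 0.277. At k = 0.28 power is at most 79%, and at k = 0.30 at most 73%. The plan's 0.173 is a CV of prevalence; nothing is given for the rate.

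**The case against.** The strongest reply is that nothing was miscalculated. From the plan's inputs, heat illness needs 63–72 households before attrition and quality of life 60, so the ranking sentence is true of the calculation performed. That stands: a reader might infer an arithmetic error, and the documents do not support it. The one-response-per-household basis is itself inferred from the reproduction.

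Second, a condensed article may leave household size and overdispersion to the full protocol or analysis plan. That would excuse silence. This article gives a complete calculation, though, and draws a definite conclusion about which outcome sets enrolment.

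Third, the caveat about cumulative prevalence points in a helpful direction. Mean episodes per person cannot be lower than the proportion ever affected, so a higher cumulative prevalence implies a higher rate and a smaller Poisson part of the relative variance. The Statistical analysis section also foresees negative binomial models. Both points are fair, but neither covers recurrence shared within households or supplies power for the rate ratio.

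Fourth, the low-power cases are demanding: they hold the rate at 0.289 under weekly surveillance together with strong recurrence. At 1.0 episode per person, power is back above 80%. This stands too, so underpowering is a possibility and not a finding.

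**Conclusion.** The concern holds as a mismatch of unit, endpoint and effect measure. The 70–80 requirement, the 30% detectable difference and the statement that heat illness needed the larger sample belong to a household-level binary outcome that the trial does not analyse.

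With the plan's CV of 0.173 and 4–8 members per household, the likely direction is that heat illness is generously sized: about 14–40 households before attrition and 89–97% power at 63, for household ICC 0.1–0.5. It is tempting to go further and say that quality of life therefore sets enrolment. The documents do not support that. The order depends on household size, household correlation, episode rate and recurrence, none of which is given, and it reverts under a low rate with strong shared recurrence. Nor does quality of life produce the stated range: its 60 households become about 67 after attrition, not 70–80.

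The risk that extra households could not repair is a between-village CV of the episode rate above about 0.28. The matter should be corrected, but it does not threaten the design on the plan's own assumptions.

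**What to change.** - Restate the heat-illness calculation for the incidence rate ratio. Use episodes per person-week, members per household (household size is already collected in the line listing), the between-village CV of the rate, within-household correlation and a stated range of overdispersion.
- Report the resulting power, or the detectable rate ratio, at the planned 22 clusters and 70–80 households.
- Drop the sentence ranking the two outcomes, or let it follow the restated figure without presuming which outcome sets enrolment.
- Bring the claim of at least 80% power for each co-primary outcome into line with the result.

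Enrolment does not change. The cost is one rewritten paragraph and possibly a less favourable power figure at the high end of the overdispersion range.

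### The heart-rate subsample figures do not agree with each other: eight adults per cluster give about 94–96% power rather than 90% by the standard calculation, and going from 8 to 10 is a 25% inflation, not 30%.

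*Protocol article*

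**What the plan says.** The Sample size section states that "a subsample of eight adults (aged 18 years to 60 years) per cluster (balanced by gender) would be required". The difference to be detected is 15% of mean heart rate, "assuming a baseline of 66±12 bpm" and, for the clustering and power, "an ICC of 0.1736 and 90% power". The trial has "11 clusters per arm (22 clusters in total"). Because more attrition is expected in this subset, the authors "have inflated the sample size by 30% to 10 individuals". The expected loss rate itself is not given as a number.

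The same section defines ICCs for continuous outcomes as between-cluster over total variance, "with total variance sourced from reference studies". For binary outcomes it works through a between-cluster coefficient of variation, k. It does not name the formula that turns the heart-rate inputs into eight.

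The subset size appears twice more. The section on data collection from the subset population gives eight participants per cluster. The Cluster randomisation section gives eight households per arm, with one adult from each.

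**The concern.** The effect, SD, ICC, power, required number, inflation and final number stand in two adjacent sentences, so a reader can check each against the others. Two checks fail. The required number looks too large for 90% power, and the final number is not the required number plus 30%.

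What is at stake is limited. Heart rate is a subset outcome outside the fixed-sequence test of the co-primaries. Still, the protocol names inconsistent use of wearables as a limitation, so the attrition allowance may well be tested. A reader of the results should be able to tell what power a given number of completers provides and how much loss the plan absorbs. The printed figures answer neither question correctly.

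**Working it through.** **Inputs from the Sample size section.** Baseline mean 66 bpm; SD 12; change 15%, so δ = 0.15 × 66 = 9.9 bpm; ICC 0.1736; 11 clusters per arm; power 90%. A two-sided 5% level is assumed: the protocol states 5% for the primary outcomes and two-sided testing at 0.05 for heat-related illness, but neither for heart rate.

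**The SD is a total SD.** The section sets the ICC as between-cluster over total variance. With total variance 12² = 144, a between-cluster variance of 25 gives 25/144 = 0.1736, the stated ICC. Were 144 the within-cluster variance, the ICC would be 25/169 = 0.148.

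**Attempt to reproduce eight.** Without clustering, each arm needs n = 2 × [12 × (1.960 + 1.282)/9.9]² = 30.88. With design effect 1 + (m − 1) × ICC and K = 11 clusters per arm:

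- m = n(1 − ICC)/(K − n × ICC) = 30.88 × 0.8264/(11 − 5.36) = 4.52, so 5.
- With K − 1 = 10 in place of 11, as a small-sample correction: 5.50, so 6.

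Neither returns 8.

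**Power at each size.** SE = 12 × √[2 × (1 + (m − 1) × 0.1736)/(11m)], with power from the normal distribution and from the noncentral t with 20 df.

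| Completers per cluster | SE (bpm) | Power, normal | Power, t (20 df) |
|---|---|---|---|
| 5 | 2.98 | 91.4% | 88.5% |
| 6 | 2.86 | 93.4% | 90.9% |
| 7 | 2.76 | 94.8% | 92.6% |
| 8 | 2.69 | 95.7% | 93.8% |
| 10 | 2.59 | 96.9% | 95.3% |

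The difference detectable with 90% power at eight is 3.242 × 2.69 = 8.7 bpm, or 13.2% of 66 (normal). With t it is about 9.2 bpm (13.9%).

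**A formula that comes nearer to eight.** Hold the between-cluster coefficient of variation constant, so that between-cluster variance grows with the mean:

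c = 1 + (1.960 + 1.282)² × [2 × σ_w²/m + k² × (μ₀² + μ₁²)]/δ²

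Here k² = 25/66² = 0.00574, σ_w² = 144 × 0.8264 = 119.0, μ₀ = 66 and, for a rise, μ₁ = 75.9.

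- m = 6: c = 11.48, so 12 clusters per arm, which is too many.
- m = 7: c = 10.87, so 11.

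Seven becomes eight if the sexes are to be equal in number. For a fall (μ₁ = 56.1), m = 5 already gives c = 10.72.

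**Do the plan's other sizes identify the method?** No.

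- Heat-related illness (28.9% against 20.23%, 80% power, 63 per cluster, i.e. 70 less 10%): the k form gives 10.98 clusters per arm. The design-effect form with one added cluster gives 11.68.
- Quality of life (SD 18, difference 4, ICC 0.015, 60 per cluster): the design-effect form with one added cluster gives 10.99.

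Each matches 11, but by a different formula.

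**Inflation.**

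- 10/8 = 1.25, so the inflation applied is 25%.
- 8 × 1.3 = 10.4, or 11 rounded up.
- If 30% is the expected loss, 8/0.7 = 11.4, so 12.
- 10 × 0.8 = 8: ten recruits keep eight completers only if loss is 20% or less.
- 10 × 0.7 = 7: at 30% loss seven remain, with 92.6–94.8% power.

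**The case against.** The strongest reply is that eight can be reached. Under the constant-coefficient-of-variation formula for a rise, the requirement is seven, and sex balance makes it eight. This stands as a possibility, and it rules out a stronger reading that a reader might infer: that six adults are needed and eight is simply wrong. Six rests on an unnamed formula and on a small-cluster correction, and it falls short under the alternative. The alternative is not shown to be the authors' method either. The protocol describes continuous ICCs as a variance ratio, not through k, and the match needs a rise; a fall needs only five.

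The second reply is that the text gives 30% as an inflation and nowhere as a loss rate, so 10 is just 10.4 rounded down. That is fair on the wording, and it means a shortfall against a promised 30% loss cannot be charged. But a required minimum is rounded up, and the inflation actually applied is 25%.

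The third reply is that oversizing harms nothing. That also stands. A reader might infer that the comparison is underpowered, or that field teams would misreport a shortfall. The first is contradicted by the power at seven completers. The second has no basis in the protocol, which sets no threshold for completers.

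**Conclusion.** The heart-rate figures are mutually inconsistent, in two small ways. By the standard design-effect calculation, eight completers per cluster give about 94–96% power rather than 90%, and 90% power is reached at five (normal) or six (t with 20 df, or the corrected formula). Because another formula gives seven or eight, the supportable conclusion is that the stated power and the stated number do not match under the usual method and that the method is not named. It is not that six is the requirement. Secondly, ten is a 25% inflation of eight, not 30%; it covers 20% loss.

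The slips offset. With ten recruited per cluster the outcome is not underpowered, even at 30% loss. This rests on 11 clusters per arm, a total SD of 12 and an assumed two-sided 5% level. It also rests on ten per cluster being what is recruited, which the two other statements of the subset size do not bear out: eight per cluster less 30% leaves 5.6, with about 90% power (t), and eight per arm would be 16 people in all. Severity is minor.

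**What to change.** Change the wording of the Sample size section; no extra participants are needed.

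1. Name the formula, significance level and sidedness used for heart rate. Then either state the power at eight completers per cluster (about 94–96% for 9.9 bpm by the design-effect method) or state the difference that eight detects with 90% power (about 8.7 bpm, 13%, normal formula). If a constant coefficient of variation was used, say so, and give the direction of change. Do not substitute six as the required number.
2. Replace the 30% with the true figure: ten recruits are a 25% inflation and cover 20% loss. Alternatively, give 30% as the expected loss and say that ten recruits then leave seven, with about 93–95% power.
3. Use one reconciled subset size, per cluster, in the Sample size section, the Cluster randomisation section and the section on data collection from the subset population, and say whether it counts recruits or completers.

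The cost is a few edited sentences.

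### The stated ±9-unit spread cannot produce both continuous-outcome ICCs (0.015 and 0.1736), so the basis of the quality-of-life power claim needs reconciling

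*Protocol article*

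**What the plan says.** All the statements are in the Sample size section of the protocol article.

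- Quality of life: the reference study "documented an average score of 68 (18.0) to detect a difference of 4 points in quality of life score assuming an ICC of 0.015", and "with 11 clusters per arm 60 households per cluster are required".
- Heart rate in the subset: baseline 66±12 bpm, with "an ICC of 0.1736 and 90% power".
- Heat-related illness: prevalence 28.9%, ICC 0.0122, derived from an "assumed cluster-level prevalence variation of ±10"% through ICC = k²P/(1−P), where k is the between-cluster coefficient of variation.
- Continuous outcomes: the ICC is between-cluster variance over total variance, with "total variance sourced from reference studies and a minimum between-cluster difference of ±9 units assumed". The section does not say how the ± figure becomes a standard deviation.
- Power: "Each co-primary outcome is independently powered at 80% or above". On the enrolment target, "the final enrolment target was set at 70–80 households per cluster, which also provides adequate power for the quality-of-life outcome".
- The section also calls the quality-of-life calculation conservative, on the ground that three visits a year over 2 years will be combined in a mixed model.

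**The concern.** One spread and one rule are stated for continuous outcomes, so quality of life and heart rate should share the same between-cluster variance. They do not, and the stated derivation is therefore wrong for at least one of them. That conclusion needs no assumption about how ±9 was converted.

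It matters because quality of life is a co-primary outcome and its power depends strongly on the ICC when there are only 11 clusters per arm. A reader cannot tell whether ±9 is a slip in the text or the real planning assumption. In the first case the power claim stands. In the second the ICC used is about a quarter of what the assumption implies.

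**Working it through.** **Inputs (all from Sample size).** Quality of life: SD 18 (variance 324), difference 4, ICC 0.015, 11 clusters per arm, m = 60 (target 70–80). Heart rate: SD 12 (variance 144), ICC 0.1736. Heat illness: P = 0.289, ICC 0.0122. Two-sided 0.05; for quality of life the two-sidedness is my reading.

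**1. The plan's own figure reproduces.** Effective n per arm = 11m/[1+(m−1)ICC]; SE = 18√(2/n).
- At ICC 0.015 and m = 60: design effect 1 + 59×0.015 = 1.885; n = 660/1.885 = 350.1; SE = 1.36; 4/1.36 = 2.94. Power is 83.7% (normal) or 79.9% (t, 20 df).
- Required m: individually randomised n = 2×(18×2.80/4)² ≈ 318. With one cluster per arm added for small numbers (10 effective), m = 318×0.985/(10 − 318×0.015) ≈ 59.8. The t version gives 60.4. The stated 60 is right for ICC 0.015.

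**2. Between-cluster SD implied by each continuous ICC.**
- Quality of life: 0.015×324 = 4.86, SD 2.20 (±4.4 at 2 SD).
- Heart rate: 0.1736×144 = 25.0, SD 5.0 (±10 at 2 SD).

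The variances differ about fivefold (25/4.86 = 5.1), so one ±9 with one divisor cannot give both.

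**3. Which conversion fits.**
- Binary, ±10 points halved: (0.05/0.289)²×0.289/0.711 = 0.0122, a match.
- Heart rate, ±10 halved: 25/144 = 0.1736, a match. ±9 halved would give 20.25/144 = 0.1406.
- Quality of life from ±9:

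| Divisor | Between-cluster SD | ICC |
|---|---|---|
| 1 | 9 | 0.25 |
| √3 | 5.20 | 0.083 |
| 1.96 | 4.59 | 0.065 |
| 2 | 4.5 | 0.0625 |
| 3 | 3 | 0.028 |
| 4 | 2.25 | 0.0156 |

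Only a divisor of 4 comes near 0.015, and that treats 9 as the whole range (±4.5). Dividing the stated half-widths by 4 would give 0.003 for the binary ICC and, from ±9, 0.035 for heart rate, so it fits neither.

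**4. Quality-of-life power for 4 points, unadjusted, single visit.**

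| Reading | ICC | Power, m = 60 | Power, m = 70–80 |
|---|---|---|---|
| As stated | 0.015 | 84% (t: 80%) | 86–88% (t: 83–85%) |
| Range of 9 (±4.5) | 0.0156 | 83% (t: 79%) | 86–88% (t: 82–84%) |
| ±9 as ±2 SD | 0.0625 | 46% (t: 43%) | 47–48% (t: 44–45%) |

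At ICC 0.0625 and m = 60: design effect 1 + 59×0.0625 = 4.69; n = 660/4.69 = 140.8; SE = 2.145. The difference detectable with 80% power is 2.80×2.145 = 6.0 points (5.9 at m = 80). With unlimited households per village, power reaches only 55%. If ±9 is read as ±3 SD (ICC 0.028), power is 70–74% for m = 60–80.

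**5. Repeated visits.** Averaging 3–6 visits, with an assumed within-person correlation of 0.3–0.7 and a persistent village effect, raises power at ICC 0.0625 only to about 48–52% (m = 60–75). The village component is not averaged down.

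**The case against.** A reader might infer that quality-of-life power is near 47% rather than 80%. The documents do not support that as a flat statement, for three reasons.

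- The divisor of 2 is inferred. It reproduces heart rate only if ±9 is replaced by ±10, so under this divisor ±9 yields neither continuous ICC. That is as much evidence against the ±9 wording as against 0.015.
- A harmless reading exists. The binary ICC is described as coming from a range, and range/4 fits it (20/4 = 5 points). If 9 is the full range between clusters and the ± sign is a slip, the same rule gives 2.25²/324 = 0.0156. That rounds to 0.016 rather than 0.015, but it is close, and the power claim survives. This reading still does not give the heart-rate ICC, which needs a range of 20.
- The 46–48% is for an unadjusted comparison at one visit. Statistical analysis plans adjustment for baseline outcome values where available, and the survey tool has a quality-of-life section. Baseline adjustment can remove persistent village differences. As an illustration at ICC 0.0625 and m = 60, assume an individual autocorrelation of 0.5, so that the correlation of cluster means is r = 0.8π + 0.2×0.5 and the variance is multiplied by 1 − r². Power is then 58% at a cluster autocorrelation π of 0.5, 70% at 0.7, 79% at 0.8 and 90% at 0.9 (53%, 65%, 75% and 87% with t). The protocol gives no autocorrelations, so these are assumptions.

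All three points stand as limits on the consequence. None removes the contradiction, and the protocol's own argument for being conservative cites repeated visits, not baseline adjustment.

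**Conclusion.** The derivation as printed is wrong for at least one continuous ICC: ±9 cannot give between-cluster SDs of both 2.2 and 5.0. This follows from the document's own figures alone.

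The sample-size arithmetic is sound once ICC 0.015 is granted. The effect on power is conditional. If the spread used for quality of life was about ±4.5, the claim of 80% stands at the enrolled 70–80 households. If ±9 was meant as about ±2 SD, unadjusted single-visit power is about 46–48% (43–45% with t), with a detectable difference of about 6 points. The document does not settle which was meant. Nor does it quantify what baseline adjustment would recover, so a power shortfall is possible but not established. The appeal to repeated visits does not answer the question, because those visits leave persistent between-village variance in place.

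**What to change.** 1. State the conversion from spread to between-cluster SD once (for example, half-width divided by 2) and apply it to all three ICCs.
2. Give the heart-rate spread separately; ±10 reproduces 0.1736 under that conversion.
3. For quality of life, do one of two things. Either correct ±9 to the spread actually used (about ±4.5, that is, a range of 9, ICC 0.0156), leaving the power claim in place. Or keep ±9 and restate the ICC (0.0625 under halving), the power and the detectable difference, showing any gain from baseline adjustment under stated autocorrelations.
4. Qualify the sentence that calls the calculation conservative: repeated visits reduce within-person variation, not persistent between-village variance.

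The cost is a text correction and, under the second option, possibly a less favourable stated power. No added clusters or change to the analysis are asked for.
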